### Analysis of secondary outcomes

The AUDIT and AUDIT-C, LDQ and RCQ scores will be summarised using descriptive statistics: means with 95% confidence intervals (or medians with inter-quartile ranges if non-normally distributed) at baseline, 12 weeks and 6 months. Change from baseline at 12 weeks and at 6 months post treatment will be presented. The hypothesis of no difference between the two treatment arms at 12 weeks and 6 months (separate analyses) will be tested using analysis of covariance (ANCOVA), controlling for baseline measurements. A p-value of 0.05 (5% level) will be used to declare statistical significance and 95% confidence intervals of the estimated effects will be reported. Time by treatment interaction will be assessed. This analysis using ANCOVA will not adjust for any missing data. However, reasons for missing outcome data will be reported and a sensitivity analysis will be undertaken Time by treatment interaction will be assessed. The mean (standard deviation) or median (inter-quartile range) of quantity and frequency of alcohol consumed in UK units per drinking day will be computed depending on whether it is skewed or not, and compared across treatment groups at 12 weeks and at 6 months post treatment using a t-test or Mann Whitney U test. The number of ED attendances is also similarly analysed. Summaries of length of stay in hospital will be presented as means (standard deviations) or medians (inter-quartile ranges) depending on whether it is normally distributed or not, and compared across treatment groups. Laboratory parameters will be summarized using means, standard deviations, confidence intervals, and ranges. Additional summaries of the data included plots of mean (±SE) values over time and scatter plots of pre- vs. post-treatment values. Change from baseline and at 12 weeks and at 6 months post treatment will be presented. A formal test of a treatment-covariate interaction will be conducted by including the interaction term in a regression model. Exploratory analysis will be conducted as to the impact on any treatment effect of other factors such as gender or age. A p-value of 0.05 (5% level) will be used to declare statistical significance and 95% confidence intervals of the estimated effects will be reported.

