## Methods/Design

### Hypothesis

EBIs delivered to alcohol-dependent patients in a hospital setting by an ASN will be effective when compared to usual care in reducing overall alcohol consumption and improving on the standard measures of alcohol dependence.

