### Secondary outcome measures

The secondary outcome measures are:

1. A change in AUDIT score from baseline at 12 weeks and at 6 months post randomisation. Although AUDIT is a screening test for alcohol use disorders [41], in common with other studies, we will in this context use it as both an outcome measure and a pre-screen to establish presence of alcohol dependence. The sum of the items scored has been used in several studies to indicate dependence and therefore will allow for comparability with other trial baseline and outcome measures [10].

2. Measure of alcohol dependence utilising the Leeds Dependency Questionnaire (LDQ) [42] at baseline, 12 weeks and 6 months post randomisation. The LDQ is a 10-item questionnaire designed to measure dependence upon a variety of substances including alcohol. The questionnaire includes 1 item from 10 markers that define dependence; these include pre-occupation, salience of alcohol, compulsion to start, planning around alcohol consumption, maximize effect, narrowing of use of repertoire, compulsion to continue, primacy of effect, constant state and cognitive set. Each item is scored 0-1-2-3, giving a maximum of 30 with higher score indicating greater degree of dependence.

3. Quantity and frequency of alcohol consumption in UK units per drinking day at baseline, 12 weeks and 6 months post randomisation.

4. Readiness to Change Questionnaire (RCQ) at baseline, 12 weeks and 6 months post randomisation. This is an important measure for non-treatment seeking populations as it has been demonstrated that treatment-seeking is an indication of treatment readiness, which has been seen as important in achieving treatment outcomes [20]. Using this measure will help us to investigate if treatment readiness does indeed have any bearing on treatment outcome in the population and setting.

5. Number of ED attendances 6 months pre and 6 months post treatment/control.

6. Hospital length of stay sum days in hospital 6 months pre and 6 months post randomisation.

7. Number of hospital admissions 6 months pre and 6 months post randomisation.

8. Length of stay for initial treatment in days.

9. Biochemical indicators of co-morbid conditions including Gamma-glutamyl transferase (GGT), Alanine aminotransferase (ALT) and mean corpuscular volume (MCV), when available will be extracted from a recent laboratory records; this is defined as the last available value prior to randomization.

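### Alcohol consumption (and, on the natural reading, ED attendances) is tested without the baseline values the trial collects: valid, but less precise than it need be

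*Protocol article*

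**What the plan says.** The protocol article's Secondary outcome measures section lists "Quantity and frequency of alcohol consumption in UK units per drinking day at baseline, 12 weeks and 6 months post randomisation" and "Number of ED attendances 6 months pre and 6 months post treatment/control". A pre-randomisation value is therefore available for both outcomes.

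Analysis of secondary outcomes has AUDIT, AUDIT-C, LDQ and RCQ "tested using analysis of covariance (ANCOVA), controlling for baseline measurements". Analysis of primary outcomes does the same for SADQ. Consumption is treated differently: it is summarised by mean or median according to skewness and "compared across treatment groups at 12 weeks and at 6 months post treatment using a t-test or Mann Whitney U test". The next sentence adds: "The number of ED attendances is also similarly analysed".

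The Hypothesis section says the intervention will be effective "in reducing overall alcohol consumption and improving on the standard measures of alcohol dependence". Reducing consumption is also the first study objective.

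**The concern.** The protocol chooses a method here, so this is not a detail left to an analysis plan. A later plan would have to depart from the wording. The choice sets aside a covariate that the trial measures anyway and adjusts for on its other scores, and no reason is given for the difference. Skewness is not a sufficient reason, because the primary-outcome section already plans a transformation when ANCOVA assumptions fail.

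Precision is at stake on an outcome named first in the hypothesis, in a trial that expects to lose half its patients. A Mann-Whitney test used alone also yields a p-value without an obvious effect size, although the section promises confidence intervals for estimated effects.

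**Working it through.** **1. Is there a baseline-adjusted comparison elsewhere?** Three other items in Analysis of secondary outcomes involve baseline:
- Changes from baseline are to be presented, which is descriptive.
- Pre/post scatter plots are descriptive too.
- A treatment-covariate interaction regression names neither outcome nor covariate, and it tests effect modification.

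None of these is a baseline-adjusted test of consumption or ED attendances.

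**2. Number analysed.** Sample Size calculation gives 51 per group for analysis. Using 53% vs 22%, two-sided 5%, 90% power and pooled variance:

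n = [1.96·√(2·0.375·0.625) + 1.2816·√(0.53·0.47 + 0.22·0.78)]² / 0.31² = (1.342 + 0.831)² / 0.0961 ≈ 49.1, so 50 per group.

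This agrees with the stated 51 to within one patient. The figure is borrowed only as a plausible number of patients interviewed at 6 months. The other pair of rates printed in that section is a separate matter.

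**3. Linear ANCOVA against a t-test.** With correlation r between baseline and follow-up, the variance of the arm difference is multiplied by 1 − r², and 51 per arm acts like 51/(1 − r²). Power at an assumed standardised difference of 0.5 is Φ(0.5/√(2(1 − r²)/51) − 1.96). At r = 0 this is Φ(2.52 − 1.96) = 71%. The document gives no r, so a range is shown.

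| Assumed r | 1 − r² | Acts like n per arm | Power |
|---|---|---|---|
| 0 (t-test) | 1.00 | 51 | 71% |
| 0.3 | 0.91 | 56 | 75% |
| 0.5 | 0.75 | 68 | 83% |
| 0.7 | 0.51 | 100 | 94% |

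**4. Skewed data, where Mann-Whitney would be used.** The 1 − r² factor does not describe Mann-Whitney, so power was simulated. Assumptions: log-normal units, log-SD 0.8, a shift of 0.5 SD on the log scale, r on the log scale, 51 per arm, 3000 replicates per setting.

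| Assumed r | t-test | Mann-Whitney | Rank-ANCOVA | Log-ANCOVA |
|---|---|---|---|---|
| 0.3 | 58% | 68% | 72% | 74% |
| 0.5 | 58% | 67% | 79% | 82% |
| 0.6 | 59% | 69% | 85% | 88% |

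With no true difference, rejection rates lay between 3.9% and 5.4% for all four methods. The Monte Carlo error is about 0.9 points (√(0.67·0.33/3000)). A repeat at r = 0.5 gave 69%, 77% and 80% for Mann-Whitney, rank-ANCOVA and log-ANCOVA.

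**5. Does the scale matter?** Yes. ANCOVA on raw skewed units with robust errors reached 64% at r = 0.5, against 69% for Mann-Whitney. At log-SD 1.0 the figures were 58% against 68%. At r = 0.3 (log-SD 0.8) raw ANCOVA also lost, 59% to 69%; at r = 0.7 it won, 79% to 70%. The gain is reliable only if a skewed outcome is analysed on a log or rank scale.

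**6. ED attendances.** No size is calculated. The document gives no rate, dispersion or correlation, and neither the 1 − r² factor nor the 51 per arm carries over. Under Data collection/management process (Economic), hospital use is retrieved from electronic records, so these counts need not suffer interview dropout.

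**The case against.** The strongest reply is that nothing here is invalid. Randomisation makes the unadjusted comparison unbiased, the significance level is kept, and chance imbalance is already reflected in the standard error. These are secondary outcomes, and the gain is small if r is 0.3 or less. All of that stands; the point is one of efficiency and consistency.

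Several stronger readings are tempting but are not supported:
- **That ED attendances are certainly compared on follow-up counts alone.** This is the natural reading, but the outcome is defined as pre and post counts, and the brief cross-reference does not exclude a pre-post change.
- **That ED windows differ between arms.** This needs the words in "Number of ED attendances 6 months pre and 6 months post treatment/control" to mean the end of treatment. They can equally mean allocation to either arm. The same section of the article counts admissions and bed-days from randomisation, and the analysis section loosely says post treatment for outcomes timed from randomisation.
- **That Mann-Whitney contradicts the promised confidence intervals.** A Hodges-Lehmann shift with an interval can accompany it. It is simply not specified, and it suits sparse, tied counts poorly.
- **That ED use dominates the costs.** Economic Evaluation lists A/E attendances, GP attendances and bed-days without ranking them.

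**Conclusion.** The point holds as a loss of precision in a stated method, most clearly for consumption. Against a t-test, the variance given up is 9%, 25% or 49% at assumed r of 0.3, 0.5 or 0.7. Against Mann-Whitney with skewed data, 51 per arm and r = 0.5, power is about 69% where rank- or log-ANCOVA would give about 77-80%.

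These sizes rest on an assumed correlation, an assumed 0.5 SD effect and log-normal data without zeros. The Background cites a study in which 30% of dependent patients stayed abstinent for 6 months, so zeros are likely and would change the figures. For ED attendances the direction of the argument is the same, but no size can be given. A reader might infer bias or an inflated error rate; neither follows.

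**What to change.** - **Consumption:** analyse units at 12 weeks and at 6 months by ANCOVA adjusted for baseline units. If the data are skewed, use a log (or log(x+1)) or rank scale, not raw units. Report the adjusted estimate with its 95% CI, and state how abstinent patients are scored. Keep Mann-Whitney as a sensitivity analysis.
- **ED attendances:** use a count model, for example negative binomial, with the 6-month prior count as covariate. Report a rate ratio and 95% CI.
- **Wording:** reconcile the ED window with the admissions and bed-day windows, so that both arms are counted from randomisation.

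The cost is a change of wording in the protocol or analysis plan. All the baseline values are already collected.

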### Missing data and missing questionnaire items

To investigate how sensitive the results of the primary and secondary analysis are to missing data a number of strategies will be used including joint modelling as well as imputing values for missing longitudinal scores at 12 weeks and 6 months. The results of the sensitivity analyses will be compared to assess the relative effect of missing data on the conclusions of the primary and secondary analysis.

For a scale which is based upon a number of items, of which one or more is missing, to investigate how sensitive the results of the primary analysis are to missing data a number of strategies will be used including a simple imputation where we will estimate the scale score for the missing items from the mean of those items which are available and this mean is then used to replace the two missing values. Missing scale scores will also be imputed with worst-case value, with best-case value and model-based imputation.

### Analysis of patient experience

The qualitative study adopts an approach based on the analytical principles of Grounded Theory. Themes and patterns in the data are identified using constant comparative techniques and data are organised into codes and categories to enable theory to be developed at a substantive level. While the constant comparative method is associated with the principles of grounded theory, comparison represents a central analytic process in inductive qualitative analysis that seeks to derive concepts from data. In analysis the researcher is as interested in 'negative', 'deviant' or 'anomalous' evidence as the identification of patterns of response. In this sort of analysis divergence provides an important way of informing and modifying emergent conceptualisations and explanation.

### Analysis of Health Economic measures

The economic analysis is designed to determine cost effectiveness for delivery of the clinical intervention protocol. This will include analysis of post intervention healthcare utilisation, and standard measures of changes in health status.

## Discussion

This paper presents a protocol for a RCT of EBI delivered to alcohol dependent patients by an ASN within an ED. Importantly; the trial will also seek to understand patients' perceptions and experiences of being part of a RCT and of receiving this form of intervention. Determining the clinical and cost effectiveness of the intervention will help inform service design and planning.

## Abbreviations used

(ASN): Alcohol Specialist Nurse; (AUDIT): Alcohol Use Disorders Identification Test; (AUDIT - C): Alcohol Use Disorders Identification Test - Community; (BI): Brief Intervention; (CRF): Case Report Form; (DH): The Department of Health; (EBI): Extended Brief Interventions; (ED): Emergency Department; (GP): General Practitioner; (ITT): Intention to treat; (LDQ): Leeds Dependence Questionnaire; (NR): Natural recovery; (PEQ): Patient Experience Questionnaire; (QR): Qualitative Researcher; (RCT): Randomised Control Trial; (RCQ): Readiness to Change Questionnaire; (SADQ): Severity of Alcohol Dependence Questionnaire;
